## Abstract

**Background:**

Problem drinking is an important global health concern, causing premature mortality and morbidity. Only few problem drinkers seek professional care, unfortunately, because of multiple barriers such as insufficient change motivation, fear of stigmatization or limited access to care. The aim of this study will be to examine the effectiveness of a novel Internet intervention termed *Vorvida*, which was developed based on established cognitive-behavioral therapy techniques with the aim of reducing problematic alcohol consumption.

**Methods/Design:**

A two-arm randomized control trial (RCT) will be conducted to determine whether using Vorvida results in greater reductions in self-reported problem drinking, compared with a care-as-usual/waitlist (CAU/WL) control group. There will be a baseline assessment (t0) and follow-up assessments after three (t1) and six months (t2). Inclusion criteria will be: minimum age of 18, an average consumption of alcohol >24/12 g (men/women) per day and an AUDIT-C score ≥ 3, as well as informed consent. Participants will be randomly assigned to the intervention or control condition at a ratio of 1:1. Recruitment, informed consent, randomization and assessment will be Internet-based. Primary outcome will be change in self-reported alcohol consumption between t0 and t1. Secondary outcomes will be self-reported drinking behavior, expectancies of effects of alcohol use, abstinence and relapse tendencies, self-efficacy and motivation to change.

**Discussion:**

This study is expected to establish the extent to which a novel Internet intervention could contribute to reducing problem drinking among adults with mild to severe alcohol use disorders who may or may not seek or access a traditional treatments. Potentially, this program could be an effective and efficient tool to help reduce problem drinking on a population level because a great number of users can be reached simultaneously without adding burden to treating clinicians.

**Trial registration:**

German Clinical Trial Registration (DRKS): DRKS00006104. Registered 14 April 2014.

## Background

Over recent decades alcohol misuse has become a major public health problem. Problematic alcohol consumption is continuing to increase and the harms associated with it are severe [1]. The World Health Organization (WHO) reported that individuals above 15 years of age consume an average of 6.2 l pure alcohol each year. Major worldwide variation has been reported, with people living in Russia and Eastern Europe consuming the most alcohol [1, 2]. In Germany, consumption is significantly above the global average, with 9.6 l pure alcohol per year and inhabitant [3, 4]. About 3.4 Million Germans meet criteria for harmful drinking or alcohol dependence while at least 10 million people in Germany are considered to be above the threshold of low-risk consumption and, therefore, engage in hazardous drinking [3–5]. Excessive alcohol consumption causes harm on an individual and societal level. It has been identified as being an important cause for premature mortality and morbidity [1]. Furthermore, excessive alcohol consumption can be regarded as an essential risk factor contributing to the global burden of disease and injury. About 4 % of all deaths and 5 % of disability adjusted life years worldwide are associated with harmful use of alcohol [1, 6]. With approximately 26.7 billion euro per year, the economic impact of alcohol-related diseases is substantial [3].

Although a variety of effective interventions are available and have been shown to be effective, only few problem-drinkers seek professional help [7, 8]. Indeed, alcohol abuse and dependence may have the widest treatment gap, compared with other mental disorders, given that 78 % of affected individuals do not receive treatment [9]. Moreover, stigmatization of people with alcohol dependency may be more severe compared to some substance-unrelated mental disorders because those affected are often regarded as more responsible for their condition; they evoke more social rejection and negative feelings, and their risk for structural discrimination is particularly high [10]. Moreover, motivation to change among many of those with harmful alcohol use is notoriously difficult and can function as a treatment barrier.

In order to overcome barriers associated with traditional formats of treatment and extend existing approaches, internet-based interventions have gained popularity over the past decade [11]. Internet-based interventions have the potential of reaching large parts of the population and allow a high degree of flexibility because they can be used at nearly any time or place, given the widespread availability of mobile Internet devices, such as smartphones. Furthermore, barriers such as privacy concerns and fear of being stigmatized or labeled as an alcoholic could be overcome by the anonymity of Internet-based interventions [12–14]. Current findings clearly indicate there is a high demand for Internet interventions in the general public [15]. A current meta-analysis of Riper and colleagues [16] found 16 RCTs on the effectiveness of Internet interventions designed for adult alcohol misuse. The results showed a small but significant overall effect (g = 0.20, 95 % CI: 0.13–0.27, *p* = .001) for the Internet interventions. Previous meta-analysis found slightly higher effects for Internet interventions that targeted other conditions, such as depression [11, 17–19].

Compared to the considerable number of RCTs on disorders such as depression and anxiety, only few RCTs have addressed alcohol disorders [16, 18–21], and most of them included mainly student and young adult samples rather than the general adult population [14, 22]. Moreover, most of the RCTs included in current meta-analyses examined single-session Internet interventions [16, 22], although some authors discuss that more extended interventions could be more effective [11, 23].

In addition, many interventions described in these meta-analysis [11, 16, 22, 23] can be accessed via Internet but are severely limited in the extent to which they use the interactivity and tailoring opportunities afforded by current software technology. Essentially, some Internet interventions consist of little more than conventional self-help text, offered in the same format to all users, without few or no interactive or “responsive” program features or custom-tailoring of content [24]. Programs that use many interactive elements, tailoring of content, and responsive web-design (i.e., self-adjusting layout of a program to the characteristics of the device used, such as desktop, tablet, smartphone), should allow for more flexible use and more user engagement, which in turn might enhance the effectiveness of the intervention. Indeed, meta-analyses have shown that interactive or tailored interventions tend to outperform non-tailored interventions in trials seeking to improve health-related knowledge or change health-related attitudes and behavior [24]. “Computer-tailoring” is a technique of adaptive communication which is described as a “combination of strategies and information intended to reach one specific person based on characteristics that are unique to that person, related to the outcome of interest, and derived from an individual assessment” [25]. Some Internet interventions use this tailoring principle by continuously requesting individual user choices and then adjusting subsequent content, in a manner that simulates an individual “dialogue” between user and the program [26, 27].

The purpose of this study is to test the effectiveness of *Vorvida*, a responsive and tailored Internet intervention against a care as usual (CAU)/waitlist (WL) condition. First, we hypothesize participants in the intervention condition, compared to the control group, will report significantly greater reductions in alcohol consumption at the three month (t1) and six month time-points (t2) compared to CAU, with t1 considered to be the time-point of primary interest. Second, we hypothesize that participants receiving the intervention differ from those in the CAU condition in measures of expectancies of effects of alcohol use, abstinence and relapse, self-efficacy and motivation to change.

## Methods

### Study design

This study is conducted as a parallel-groups randomized controlled trial. Participants will be randomized into two groups: 1) Immediate access to the Internet intervention (*Vorvida* group) and 2) CAU/WL Participants in the first group will receive individual vouchers with which they can immediately begin using the program. The participants in the second group will receive their access vouchers after a delay of six months (that is, after completing the t2 online questionnaires).

### Recruitment

The sample will be recruited through multiple access ways, including health insurance companies (e.g. advertisement in newsletters or websites), care providers (e.g. advertisements at family doctors' offices, clinics, information centers), non-care providers (Internet forums, newspaper adds, panels, print media). Potential participants will be informed that they can visit a website (www.vorvida-studie.de) that contains detailed information about the study. Additionally, participants will be recruited through the German e-mental health portal www.psychenet.de.

### Study procedure

We developed a study website (www.vorvida-studie.de) to inform potential participants about the aim of the study, the procedure, data protection and possible benefits and risks of the study. Participants will be informed that they can withdraw from the study at any time without having to disclose reasons. After reading all information, electronic informed consent will be sought before the screening for eligibility. Persons willing to participate will be asked to fill out an online screening questionnaire to test if they meet inclusion criteria. Within one week, participants will receive an e-mail to inform them whether inclusion criteria are met and, if so, what next steps are required. All included participants will receive a link to the online baseline questionnaire (t0) and are asked to respond to it within one week. An e-mail reminder will be sent out after two and after four weeks to those who did not reply. After responding to the baseline questionnaire, participants will be randomized to one of the two study arms. Each participant will receive an e-mail with the randomization result. The e-mail of the participants randomized to the *Vorvida* group will contain the access key to the *Vorvida* program, a 12 digit number registration number that activates the program for 180 days after initial registration. The CAU/WL group will be informed about the waiting time of six months until they receive their access key to the program.

Three (t1) and six months (t2) after completing the baseline questionnaire (t0), participants in both groups will receive an online-link for the follow-up questionnaires. They will be asked again to respond within one week and will receive two reminder e-mails, after two and after four weeks, if they do not do so. Furthermore, participants in the *Vorvida* group will receive an e-mail reminder to encourage program use after three weeks, six weeks, nine weeks and sixteen weeks after receiving the access key.

A bias of attrition, meaning the loss of participants to the follow-up assessment is a well-known problem in RCTs, particularly of Internet interventions, and can affect the strength of the findings [28]. Because non-monetary incentives have been shown to reduce attrition in online trials [29, 30] each participant who completes the baseline questionnaire (t0) and the two follow-up questionnaires (t1 and t2) will receive a 10€ Amazon gift voucher.

The trial flow of this study is shown in Fig. 1. The results will be reported in accordance with the CONSORT E-health statement.

**Fig. 1 Fig1:**
[figure not shown]
Trail flow of the study.

### Inclusion and exclusion criteria

Preconditions to participate in the study are: e-mail access, availability of a computer, tablet or a smartphone, access to the Internet, Internet literacy, sufficient knowledge of the German language and no impairments in hearing, speech and vision.

Inclusion criteria are: a minimum age of 18, heavy drinking episodes or harmful and hazardous alcohol consumption, according to guidelines published by BZgA [5] (www.bzga.de) (an average consumption of >24/12 g (men/women) pure alcohol per day and/or an AUDIT-C score ≥ 3) [31], and informed consent. Exclusion criteria will be of suicidal ideation and/or tendency and no informed consent. See Table 1.

**Table 1 Tab1:** Inclusion and exclusion criteria.

Inclusion criteria	Exclusion criteria
Minimum age of 18	Presence of suicidal ideation and/or tendency
An average consumption of >24/12g (men/women) pure alcohol per day	No informed consent received
AUDIT-C score ≥ 3	
Informed consent received	

### Sample size

The sample size is estimated using Gpower v.3.0.5 software [32]. The calculation is based on the primary outcome measure (alcohol consumption).

Other studies on Internet self-help programs on alcohol misuse showed mainly small effect sizes between d > .2 and d < 0.4 [11, 18].

To detect effect sizes of d = 0.28, an effect derived from a meta-analysis of self-guided Internet interventions [18], with a power of 0.80 and a significance level of 0.05 to compare the *Vorvida* group with the CAU/WL group, a target sample size of N = 404 (n = 202 per group) is required. Since it is expected that 20 % of variance can be explained through baseline-covariance, adjusted effect sizes were used in this power calculation.

### Randomization

After the completion of the baseline questionnaire (t0) participants will be randomized with the ratio 1:1 to the two study arms (intervention or control group). The randomization will be conducted with a computer generated list of numbers. This list is generated by an independent researcher; the other researchers are blinded to the list, ensuring concealed allocation to conditions.

### Intervention

#### Access to the intervention

The participants in the intervention group will receive an access voucher immediately after completing t0 questionnaires, which will enable them to use the *Vorvida* program for approximately six months (180 days) after initial registration.

#### Intervention description

The *Vorvida* program was designed for people aged above 18 who consider their own alcohol consumption patterns to be problematic and are therefore seeking help on the Internet. It is intended for those with harmful and hazardous alcohol consumption patterns as well as alcohol dependence. After initial registration and accepting the program’s terms and conditions, users are asked to enter their e-mail address and set a password, which can then be used to access the personalized program on any suitable device, including smartphones and tablet or desktop computers.

*Vorvida* was produced with the broca® software, which was developed by the GAIA AG and is the basis for several other programs (e.g. deprexis) [26]. Broca uses a computer-tailoring approach in which the program interacts as an “expert” with the user, who continuously responds by choosing from a menu of predetermined options, such that a “simulated dialogue” emerges with every user. Users are addressed by a name they can set for themselves, and an attempt is made in the “dialogues” to provide personally relevant information, with the aim of increasing learning effects [33].

The users can work individually on different contents by reading short text sequences for approximately 15 to 45 min, depending on reading speed and on individual response selections and differing paths through the program content. The program’s content is based on a range of established, evidence-based cognitive-behavioral therapy techniques, which are referenced within the program, as described below. Therefore, the program is operating with different techniques to change behavior techniques, including procedures gleaned from motivational interviewing (e.g., decisional balance), goal setting, self-monitoring of symptoms with questionnaires, cognitive and behavioral strategies for handling alcohol cues, craving and risk situations. Further, cognitive restructuring, mindfulness-based methods, mental imagery and homework exercises are introduced.

The *Vorvida* program is broadly organized in four modules. The first module focuses on individual drinking patterns, e.g. clarification of intrinsic versus extrinsic change motivation [34], exploration of the perceived advantages and disadvantages of drinking [35] and education about the harmful consequences of alcohol abuse. Moreover, realistic goal setting (e.g. reduction of consumption or abstinence) is discussed in this first module. The second module focuses on coping with alcohol craving, e.g. identification of trigger cues and mind-fullness based methods for handling craving (e.g., “urge surfing”), as well cognitive reframing techniques [36]. The third module focuses on coping with risk situations, e.g. distraction techniques [37], imaginative cue exposure [38] and problem-solving techniques [39]. The fourth module focuses on dealing with slips and relapses and summarizes the content of previous modules. It discusses the achieved goals and long-term goals and provides an “emergency case” with cognitive and behavioral methods that might be used in a relapse situation [36].

Moreover, the program includes two short questionnaires, 1) a “mood-check”, which is offered daily to allow the user to monitor and reflect on mood fluctuations over time, 2) a weekly alcohol consumption check that is based on two items: a) “On how many days did you drink alcohol?” (response options: 0–7 days) and b) “How much alcohol did you drink if you drank alcohol on one day?” (response options 1 to 12 standard drinks). Users receive individual feedback on these two items, taking into account both frequency and amount of alcohol consumption, to help them monitor their alcohol use pattern.

Users can engage with the program at their own speed without the need of following a specific schedule. However, based on experiences with previous programs, it is recommended that users interact with the program for approximately two hours per week, to ensure sufficient exposure to the content but also allow enough time to apply techniques “offline” in relevant circumstances.

#### CAU/WL group

Participants of the CAU/WL group will not receive the *Vorvida* intervention for the time of the study. However, they will receive a free access to *Vorvida* six months after registering for the study and will then also be able to use the program for another six months.

Participants of both groups are free to seek any other help they need or desire, e.g. pharmacological, psychological treatment or counselling.

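### The article gives incompatible triggers for control-arm access to Vorvida, and a calendar trigger can release the program before a control answers the six-month questionnaire (t2)

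*Protocol article*

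**What the plan says.** Three sections of the protocol article describe when controls receive the program.

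- **Study design:** vouchers come "after a delay of six months (that is, after completing the t2 online questionnaires". The six-month delay and t2 completion are treated as the same moment.
- **Study procedure:** "The CAU/WL group will be informed about the waiting time of six months until they receive their access key". No start point is given and t2 is not mentioned.
- **CAU/WL group:** controls "will not receive the *Vorvida* intervention for the time of the study", but the next sentence gives them access "six months after registering for the study".

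The t2 schedule is in Study procedure. Follow-up links are sent "Three (t1) and six months (t2) after completing the baseline questionnaire (t0", a reply is requested within one week, and non-responders are reminded after two and four weeks. The same section governs what comes before t0. The eligibility e-mail follows screening within one week. The t0 questionnaire should be answered within one week of its link, and "An e-mail reminder will be sent out after two and after four weeks to those who did not reply".

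**The concern.** The triggers differ in kind. One depends on an event (t2 answered) and another on the calendar (six months from registering). They coincide only if every participant moves from registration through t0 to t2 without delay, and the article's own reminder schedule provides for delays. On the calendar rule, a control can hold the program before answering t2, contrary to the article's statement that controls go without it during the study.

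The six-month contrast is at stake. The first hypothesis, at the end of the Background, names t2 as well as t1. The secondary outcomes are analysed in mixed models with time as a repeated effect, so control t2 values enter those too. Six months is also the last time-point at which the arms are meant to differ in access. If Vorvida works, controls who start it before answering t2 shrink the difference. Exposure would also be concentrated in slow responders, so it would not be spread at random over the control arm.

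**Working it through.** The article gives no figure for this overlap, so there is nothing to reproduce first. The check is timeline arithmetic.

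**Inputs (Study procedure)**
- E = lag from screening to the eligibility e-mail: 0 to 7 days.
- B = lag from t0 link to t0 completion: 7 days requested; 28 days if the reply comes at the last reminder.
- F = lag from t2 link to t2 completion: 7 days requested; 28 days if the reply comes at the last reminder.

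**Inputs (Primary outcome measures)**
- Recall windows: 30 days for the QFI, 7 days for the TFB.

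**Reading 1: registering means sign-up or screening (assumption)**

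Access = registration + 6 months.
t2 link = registration + E + B + 6 months.
t2 answer = t2 link + F.

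The six months cancel, so access precedes the link by E + B and precedes the answer by E + B + F.

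| Case | Before t2 link | Before t2 answer |
|---|---|---|
| No delays | 0 | 0 |
| Every one-week limit just met | 7 + 7 = 14 days | 14 + 7 = 21 days |
| t0 and t2 both answered at last reminder | 7 + 28 = 35 days | 35 + 28 = 63 days |

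**Reading 2: registering means t0 completion or randomization (taken as the same day)**

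Access falls at the t2 link date, so the overlap is F alone: 0 to 28 days, and only for those who do not answer at once.

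Under both readings, replies after the last reminder would lengthen the gap.

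**Study design rule**

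If access follows the t2 answer, the overlap is zero by construction.

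**Recall windows**

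An overlap of 21 days covers the whole TFB window and 21 of the 30 QFI days. An overlap of 28 days covers 28 of the 30, and 35 days or more covers both windows fully.

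**Is t1 at risk?**

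Take three months as 91 days and six as 182. The earliest access in the table is 182 − 35 = 147 days after t0 completion. A t1 reply at its last reminder comes at 91 + 28 = 119 days. That leaves 147 − 119 = 28 days clear in the worst tabulated case.

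**The case against.** The strongest reply is that early access was never intended. Study design defines the delay by t2 ("that is, after completing the t2 online questionnaires"), the CAU/WL section says controls go without the program during the study, and only one loosely worded clause points the other way. The word registering is undefined; elsewhere in the article, registration means signing up to the program. This has force on intent and size, but it does not remove the contradiction. Even on the later reading of registering, a calendar trigger reaches late t2 responders before they answer.

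Several stronger readings are tempting and are not supported:

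- **That controls will typically hold the program for nine weeks before t2.** The 63 days need the slowest eligibility e-mail and last-reminder replies at both t0 and t2 in the same person.
- **That the dilution can be quantified**, for example by scaling down the d = 0.28 used for the sample size. That value was used to plan the primary outcome. The article does not give the share of controls who would start early or the effect of a few weeks' use.
- **That making access depend on t2 encourages response in one arm only.** Both arms get the same gift voucher and the same reminders. Later access is inherent in a waitlist, and Study design may be describing sequence rather than a condition.
- **That control answers given after access should be set to missing in the main analysis.** That discards observed data because of post-randomization behaviour and creates missingness in one arm. It also departs from the plan to use all available data from all randomized participants.

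It is also fair to say that any bias would run towards no difference, and that only the primary analysis is to be interpreted as confirmatory.

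**Conclusion.** The contradiction stands: the sections cannot all be followed as written, and a calendar rule lets controls have Vorvida before their six-month data are collected. The overlap is a range that depends on what registering means. It is 0 to 63 days before the t2 answer if registering is sign-up or screening (up to 21 if all one-week limits are met), and 0 to 28 days, for late responders only, if it is t0 completion or randomization. These ranges assume replies no later than the last reminder. The likely consequence, if the program works, is some dilution of the t2 comparisons, of a size the article does not allow one to estimate. The confirmatory t1 comparison is not affected. The point is worth correcting because it is cheap and protects a contrast named in the first hypothesis, but it does not threaten the primary conclusion.

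**What to change.** Reconcile Study design, Study procedure and CAU/WL group to one access trigger that is consistent with the article's own statement that controls do not receive Vorvida during the study. Define registering if the word is kept. State how the trigger relates to t2 collection, including what happens for controls who never answer t2. The choice of rule belongs to the investigators; the need is for a single rule. Recruitment was still open at the time of the article, so a consistent rule can still be applied to controls who have not yet reached six months.

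In the analysis, keep the as-observed intention-to-treat comparison as the main t2 result. Where access dates are available, flag control t2 records answered after access and exclude them in a sensitivity analysis only. The article does not say whether program access dates can be linked to the survey records, so this step is conditional.

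The cost is wording, the timing of one e-mail, and one sensitivity analysis.
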